## Discussion

Diet is one of the main environmental factors triggering atherosclerosis and plaque progression. In fact, the current “American Dietary Guidelines’ Key Recommendations for Healthy Eating” recommends a Mediterranean-style pattern as one of its three suggested healthy diet styles [43]. Moreover, when changes over time are assessed, improved adherence to the traditional Mediterranean-style pattern is strongly associated with reductions in all-cause mortality and cardiovascular mortality [44]. On this basis, we have designed the MEDIMACS clinical trial to understand the mechanisms involved in diet-induced changes on anatomical and functional biomarkers of coronary atherosclerosis.

Several individual nutrients have been mechanistically associated with beneficial effects on the gastrointestinal tract microbiome. However, in contrast to the isolated single-nutrient approach, the MedDiet intervention is based on current paradigms of studying overall dietary patterns. These have the advantage of taking into consideration the potential synergistic or antagonistic effects of different nutrients and better represent the dietary practices found in real-world diets [45]. The appropriateness of this intervention is also supported by well-established cardiovascular benefits in primary prevention. Although several large-scale trials using MedDiet interventions are currently ongoing, to the best of our knowledge, no trial is currently including patients in the subacute phase after an ACS.

Numerous molecular pathways have been involved in the beneficial effect of MedDiets, such as reduction in the expression of endothelial leukocyte adhesion molecules and reduction of DNA synthesis in human coronary smooth muscle cell. However, the link between MedDiet and cardiovascular protection has not been fully elucidated. Remarkably, the interplay between diet, gut and oral microbiota and the temporal changes of plaque composition and vascular function—key agents in the pathogenesis of atherosclerosis—remains largely unknown.

### Clinical impact

The combination of a well-controlled experimental intervention and complex mechanistic objectives shall provide valuable insights into protective microbiota-mediated roles in the MedDiet. Moreover, the identification of specific microbial profiles related to cardiovascular health could help to design probiotic treatments―alone or in combination with food supplements―to improve their efficacy. In addition, microbiota-based diagnostic kits to personalize and monitor cardiovascular risk could be developed. In the future, tests of microbiota-mediated markers could identify individuals at a particular cardiovascular risk who should be prioritized for prevention.

Shifting dietary patterns and directions worldwide entails substantial economic and public health efforts that are frequently in overt conflict with the major stakeholders of food companies. Further demonstrating the efficacy of MedDiet for secondary prevention in patients with CAD may help to justify the need and opportunity of clinical interventions to promote adherence to this traditional diet. Furthermore, a comprehensive view of the biological processes triggered by diet nutrients could eventually lead to the design of diet modifications based on well-established biological pathways.

### Limitations

Complying with basic ethical principles, the control group will receive standard-of-care diet recommendations which include several aspects of the MedDiet. Other alternatives, such as a low-fat diet, are associated with worse outcomes than MedDiet and would not be ethical to implement in a contemporary clinical trial [3]. We recognize that, for the purpose of MEDIMACS, adherence to MedDiet in the control group may blur the effect of the experimental intervention and decrease the power to detect differences between arms. However, it has been demonstrated that a personalized, professionalised and closely monitored high-intensity intervention is highly effective to promote adherence to traditional MedDiet, whereas general recommendations are much less powerful [20]. Therefore, we anticipate that true adherence to MedDiet specifications will be highly different between both groups. Nevertheless, primary and secondary endpoints will be analysed both by intention-to-treat and by a per-protocol basis. For this purpose, ad hoc biomarkers have been implemented and will provide investigators with robust metrics of diet adherence and efficacy.

The primary endpoint of the trial is based on intracoronary imaging, and therefore, an invasive catheterization procedure is required for obtaining this read-out. Because patients may refuse undergoing this second study, a 45% attrition has been pre-specified. A detailed plan to quantify compliance to MedDiet in both arms has been designed, including validated dietary self-reporting questionnaires and biomarkers. Biomarkers of compliance will be measured in random subset of participants from the two arms of the trial as a potential way of accommodating both systematic and random components of measurement error in dietary self-reporting.

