### Sample size

The sample size of the MEDIMACS clinical trial has been calculated on the assumption of an expected difference of 40% on the relative change in the fibrous cap thickness of the atherosclerotic plaque from baseline to 12 months between patients undergoing a high-intensity MedDiet intervention in comparison with the standard of care. This magnitude is a 10% lower than the difference previously reported using a similar design in a clinical trial comparing the effect on the fibrous cap of lipid-lowering therapy with 5 mg/day versus 20 mg/day atorvastatin, with an estimated standard deviation of 58% [37]. Based on a two-sample bilateral alpha error of 0.05 and a power of 0.80, the required number of patients is 35 per group. Assuming an attrition rate of 10%, 100 patients are needed to be randomized following a 1:1 allocation ratio. With this sample size, different scenarios could be contemplated under potential deviations from the expected effect size (Table 2).

**Table 2 Tab2:** Alternative scenarios for statistical power with *n* = 100 sample size, assuming 10% attrition rates

Effect size	Power	Comment
50%	100%	Effect addressed in EASY-FIT Study
**40%**	**99.60%**	**Baseline assumptions**
30%	93.45%	Effect 25% relatively lower than expected

Regarding the suitability of this sample size to evaluate the secondary endpoints, micro- and macrovascular endothelial functions are proven to be highly sensitive to detect meaningful effects using small sample populations (50–100 patients) [38, 39]. Microbiota, immunological and metabolic changes in response to diet interventions have been widely reported using small sample populations (20–50 patients), particularly under pathological conditions [40, 41].

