### Statistical analysis plan

The primary endpoint will be analysed by intention to treat using a linear mixed-effects model accounting for repeated measures. Values of cap thickness will be entered as the dependent variable. The visit, the treatment group and their interaction will be entered as fixed effects, whereas the patient identification is entered as random effect. Thus, the coefficient of the term accounting for the interaction between the treatment group and visit provides an adjusted estimate of the magnitude of change in thickness at 1 year attributable to the effect of the intervention. The 95% confidence interval of this estimate will be assessed by asymptotic and bootstrap methods. Under a missing at random assumption, this method gives unbiased estimates of the effect. Quantitative indices of endothelial function, coronary physiology and additional metrics of plaque composition will be also analysed using linear mixed-effects models. The analysis of clinical outcomes will be conducted using the Kaplan-Meier method and the log-rank test to compare both intervention groups. Statistical comparisons will be 2-tailed and a statistical significance level of 0.05 shall be considered. Uni- and multivariate linear and non-linear mixed and regression models, adjusting for covariables, will be conducted for the relationship of microbiota composition (diversity and abundance metrics), the number and type of immune cell populations, proteins and metabolites and diet and clinical outcomes.

A modified intention-to-treat analysis including all randomized patients who undergo the catheterization procedure at a 12-month follow-up visit will be used to evaluate the primary endpoint and all secondary endpoints (*intention-to-treat analysis set*). In addition, a per-protocol analysis will be performed following recent directions for analyses of pragmatic trials to control for confounding [42] after excluding from the intervention arm those patients in whom the food frequency questionnaires and biological markers indicate low compliance to the prescribed MedDiet (*per-protocol set*). Secondary endpoints #4–10 will be analysed in all patients that complete the 12-month follow-up period regardless if they undergo the follow-up catheterization procedure or not (*full analysis set*).

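### The sample size assumes 10% attrition while the limitations call 45% pre-specified for the same endpoint; correct inflation gives 78 or 128 randomized, not 100, and at a true 45% loss power is about 71%

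*Protocol article*

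**What the plan says.** The Sample size section of the protocol article plans for "an expected difference of 40% on the relative change in the fibrous cap thickness", "with an estimated standard deviation of 58" percent. It continues: "Based on a two-sample bilateral alpha error of 0.05 and a power of 0.80, the required number of patients is 35 per group". The step to the randomized total is: "Assuming an attrition rate of 10%, 100 patients are needed to be randomized following a 1:1 allocation ratio". The caption of Table 2 uses the same rate ("sample size, assuming 10% attrition rates"), and the table prints powers of 100%, 99.60% and 93.45% for effects of 50%, 40% and 30%.

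The Limitations section, writing about the invasive procedure needed to read the primary endpoint, says: "Because patients may refuse undergoing this second study, a 45% attrition has been pre-specified".

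The Statistical analysis plan section sets the population for the primary endpoint: "A modified intention-to-treat analysis including all randomized patients who undergo the catheterization procedure at a 12-month follow-up visit".

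**The concern.** Both rates are presented as design assumptions, and both bear on the same quantity. The trial is sized on the change in cap thickness, which exists only for patients who have the second catheterization. The primary analysis set is limited to those patients. Each refusal therefore removes a patient from the primary analysis, and the mixed model cannot recover someone who is outside the set.

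The reader cannot tell how many evaluable patients were planned or what power the primary test was meant to have. This matters most if the result is null. The Limitations section already concedes that adherence to the diet in the control arm may reduce power, and a null result reads differently at 71% planned power than at 90%. A single rate fixed before the results also gives the observed attrition something to be judged against.

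**Working it through.** **Inputs**, all from the Sample size section unless noted: difference δ = 40 percentage points in relative change; SD σ = 58; two-sided α = 0.05; power 0.80; 35 evaluable per group (70 in total); 100 randomized 1:1; attrition 10%. From Limitations: attrition 45%.

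**1. The plan's evaluable number.** By the normal formula, n per group = 2σ²(z₀.₉₇₅ + z₀.₈₀)²/δ² = 2 × 58² × (1.960 + 0.842)²/40² = 33.0 (33.005 unrounded, so 34). The two-sample t-test also needs 34 (power 80.0%). At the stated 35 its power is 81.2%. The figure of 35 is sound.

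**2. From evaluable to randomized.** The correct inflation is N = 70/(1 − d).

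- d = 10%: 70/0.90 = 77.8, so 78.
- d = 45%: 70/0.55 = 127.3, so 128 (68/0.55 = 123.6, so 124, if 34 per group is used).
- Working back from 100: d = 1 − 70/100 = 30%, a rate that the article does not mention.

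The common but incorrect inflation N × (1 + d) gives 70 × 1.10 = 77 at 10% and 70 × 1.45 = 101.5 at 45%. With 34 per group it gives 34 × 1.45 = 49.3, so 50 per arm. The 45% rate, wrongly applied, therefore lands close to 100; the 10% rate does not under either formula.

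**3. Power with 100 randomized.** Two-sample t-test, noncentrality δ/(σ√(1/n₁ + 1/n₂)), σ = 58. At 45% loss, 100 × 0.55 = 55 evaluable, or 27 and 28 per arm, and the noncentrality is 40/15.64 = 2.56.

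| Attrition | Evaluable per arm | Power at 40% | Difference detectable with 80% power |
|---|---|---|---|
| 10% | 45 | 89.9% | 34.6% |
| 30% | 35 | 81.2% | 39.4% |
| 45% | 27–28 | 70.9% | about 45% |

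The normal approximation gives 90.5%, 82.3% and 72.5%. By the t-test, 80% power holds up to about 32% attrition, which leaves 34 per arm.

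**4. Table 2 against its own caption.** Same t-test, SD 58%.

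| Effect | Printed | 10% attrition (45 per arm) | 45% attrition (27–28 per arm) |
|---|---|---|---|
| 50% | 100% | 98.1% | 88% |
| 40% | 99.60% | 89.9% | 71% |
| 30% | 93.45% | 68.0% | 47% |

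The printed values lie close to those for 90 patients per arm (99.6% and 93.2% at effects of 40% and 30%), which is the whole evaluable trial at 10% attrition counted as a single arm. They also match a one-sample calculation with 45. Either origin is an inference. What can be said firmly is that the printed powers do not follow from the stated inputs, so the table cannot show that power is ample at 45% loss.

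**The case against.** The strongest defence is that the two rates may describe different losses. The Sample size section does not say what is lost at 10%, and the Statistical analysis plan section distinguishes patients who complete 12 months from those who also undergo catheterization. So 10% could be loss to follow-up and 45% refusal of the procedure. This stands to the extent that the right repair may be to label two rates. It does not rescue the calculation: the trial is sized on an endpoint that needs the catheterization, so the refusal rate governs the evaluable number.

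A second defence is that 45% was a recruitment margin over the required 70, since 100/70 = 1.43. The tolerated loss would then be about 30% and the power about 81%. This is possible, but the Limitations section calls the figure attrition and links it to refusal, and a margin is not the same thing as a loss fraction. The reading does mean that the 71% must stay conditional.

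A reader might infer that 100 has no connection with either rate. That is too strong, because 70 × 1.45 = 101.5 is close to 100 and suggests that 45% was the planning rate and the 10% a misstatement. This origin is not stated, and the method behind it is wrong. If it is the true origin, it also explains why 100 falls short at 45%.

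Finally, the calculations use a two-sample t-test on relative change, with an SD taken from a cited trial, whereas the primary analysis is a mixed model on cap thickness. The t-test is the comparison that the article's own calculation describes, so it is the fair check on that calculation. Power under the mixed model could differ somewhat.

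**Conclusion.** The contradiction is real and unreconciled, and it concerns the sample-size justification of the primary endpoint. The stated total of 100 does not follow from 10% attrition, and it follows from 45% only by an incorrect inflation. If 45% is the true expected loss, about 55 patients are evaluable against the 70 required, power for a 40% difference is about 71%, and the difference detectable with 80% power is about 45%. The stated 80% is then not met. If 10% is right, 78 randomized would have been enough and 100 gives about 90%. These figures assume SD 58%, a two-sample t-test and equal loss in the two arms.

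A reader might go further and infer that the power is undefined, that the trial is underpowered whatever the attrition, or that the primary estimate is compromised. The documents do not support this. Across the two stated rates, planned power lies between about 71% and 90%. The shortfall depends on 45% being a true loss fraction. The choice of rate changes neither the estimator, nor the alpha, nor the definition of the analysis set.

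**What to change.** State one attrition rate for the primary endpoint in the Sample size section, the Limitations section and the Table 2 caption. If 10% was meant as loss to follow-up, label it so and keep it separate from refusal of the second catheterization. Beside the chosen rate, give what it implies for the fixed 100 randomized:

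- **45%:** about 55 evaluable, about 71% power for a 40% difference, about 45% detectable with 80% power.
- **10%:** 90 evaluable, about 90% power, about 35% detectable, with a note that 78 would have sufficed for the stated requirement.

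Recalculate the Table 2 powers at the same rate for effects of 50%, 40% and 30%: about 98%, 90% and 68% at 10% attrition, or about 88%, 71% and 47% at 45%, in place of 100%, 99.60% and 93.45%. Changing the caption alone would leave the table in conflict with the restated power.

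The cost is limited to restating figures. Recruitment is complete, so no further enrolment follows, and the analysis is unchanged.

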## Trial status

Protocol version 4.0. Date: November 10, 2018

Date recruitment started: May 14, 2019

Recruitment completed: August 2, 2021

Recruitment status: Completed

## Data Availability

Data generation and analysis procedures follow the FAIR data management principles of Findability, Accessibility, Interoperability and Reusability. An eCRF has been built, using a collaborative platform (RedCap) administered by the principal investigator, in which all demographic, analytical and clinical data will be stored. A sequential code number will be automatically assigned to each participant. Personal data will not be included in the research database. Confidentiality of patient data will be maintained throughout the study; the list of codes for each participant will be stored securely and will be accessible only to the principal investigator. Trial data will be accessible only to the research team. An in-house certified research nurse not participating in the study is dedicated to external monitoring following Standard Operating Procedures. Sequences, genotypes and protein and immune profiles will be organized and indexed in metadata files following a unique code of assignment that will be submitted for releasing to public database repositories such as GenBank, Gene Expression Omnibus and ClinicalTrials.gov, following the International Standards for Genomes and Metagenomes. MEDIMACS researchers embrace the values of openness and transparency in science and will publish the results of this study within 6 months after trial completion. The datasets generated and/or analysed during the current study will be made available upon request to the investigators and after approval by all the members of the MEDIMACS consortium.

## Abbreviations

ACS: Acute coronary syndrome
TMAO: *N*-oxide trimethylamine
MedDiet: Mediterranean diet
EVOO: Extra-virgin olive oil
FFQ: Food frequency questionnaire
MEDAS: Mediterranean Diet Adherence Screener
OCT: Optical coherence tomography
MACE: Major adverse cardiovascular events
